### Trial surgical interventions

The intervention arm will receive MVr via minimally invasive thoracoscopically guided right minithoracotomy. The control group receive MVr via conventional sternotomy.

### Intervention arm

The patient is intubated with a single or double lumen endotracheal tube. Cardiopulmonary bypass is established by femoral artery cannulation and venous return achieved from the venae cavae using a single bicaval cannula placed from the femoral vein, or with an additional cannula in the superior venae cava. Transoesophageal echocardiography confirms the optimum location of the venous and arterial cannulas.

A 4–7 cm right lateral minithoracotomy is then used to enter the thorax through the third or fourth intercostal space. A soft-tissue retractor, with or without a small thoracic retractor, is used to spread the ribs. The pericardium is opened 3–4 cm anterior and parallel to the phrenic nerve from the distal ascending aorta to the diaphragm. A video camera is inserted through a 5–10 mm port.

Endoballoon occlusion, or a transthoracic clamp, achieves aortic occlusion. Cardiac arrest is achieved with repeated doses of cardioplegia. The mitral valve is approached through a paraseptal incision and a left atrial retractor is used to expose the mitral valve.

Following the mitral valve procedure, the left atrium is closed, the heart deaired and aortic occlusion removed. Cardiopulmonary bypass is then discontinued and the thoracotomy incision closed once haemostasis has been achieved.

### Control arm

The sternum is divided completely (from the collarbone to the bottom of the breastbone) and cardiopulmonary bypass established by siting cannulas in the right atrium and inferior venae cava and ascending aorta.

Cardiac arrest is achieved with cardioplegia and the mitral valve approached via the left atrium. The valve is repaired and assessed intraoperatively by water testing. Once the repair is deemed satisfactory, the atrium is closed, deairing manoeuvres performed, and the aortic cross clamp removed to allow reperfusion of the heart. Cardiopulmonary bypass is discontinued once haemostasis is achieved and the sternum is closed.

### Outcomes

The primary outcome is physical functioning and associated return to usual activities measured by change in SF-36v2 physical functioning scale^42^ 12 weeks following index surgery using a 4-week recall period.

The primary economic outcome is cost effectiveness measured in terms of incremental cost per quality-adjusted life year (QALY) gained over 52 weeks following index surgery.

Secondary outcomes post index MVr:

Feasibility and study recruitment, explored by means of a 6-month internal pilot.Cardiac function; assessed using transthoracic echocardiography (TTE), early (1 day to 12 weeks) and late (52 weeks) by an independent core laboratory.Mitral valve and mitral valve surgery related events and survival (morbidity and mortality); compared at 52 weeks and up to 5 years using adverse event data and Hospital Episode Statistics and National Institute for Cardiac Outcomes Research data.Physical functioning and quality of life over 52 weeks; compared using SF-36v2 and EuroQol 5 Dimension 5 Level (EQ-5D-5L).^42–45^Levels of physical activity and quality of sleep; quantified using accelerometer measures (GENEActiv^46–50^) over 52 weeks.Surgical outcomes quantified over 52 weeks.Costs, including intervention-specific estimates, of the two operations and their sequalae over 52 weeks.QALYs, estimated from EQ-5D-5L^43–45^ and SF-6D (derived from the SF-36v2) over 52 weeks.Modelled costs and QALYs over the patient lifetime.Modelled incremental cost per QALY gained over the patient lifetimeHospital Episode Statistics (HES) data will be explored to understand if it adequately captures mitral valve events.

### Sample size

The primary outcome measure is change in physical functioning scale within SF-36v2^42^ from baseline to 12 weeks following index surgery. On the basis of the literature and consulting with cardiac and patient communities, a minimally clinically important difference is 10 points on the scale. UK Mini Mitral is powered to investigate the superiority of thoracoscopically guided right minithoracotomy over conventional sternotomy.

One study^31^ reports a small variation (SD of 8) in SF-36 physical function scores; this is not seen in other studies^32 33^ which report a SD of 30. We used the conservative estimate to inform the original sample size calculation:

Assuming alpha of 5% and 90% power, 382 patients (191 in each arm) would be required to detect a minimally clinically important difference of 10 points in the SF-36v2^42^ physical functioning scale at 12 weeks (assuming SD of 30); allowing for attrition, we planned to randomise 400 patients. To assess our assumptions, we performed a blinded sample size re-estimation using baseline SF-36v2 physical functioning scale data from 177 trial patients. Using the re-estimated SD of 26.3 with 90% power, 288 patients are required to detect a 10 point difference in SF-36v2 physical functioning at 12 weeks. Accounting for 10% attrition, 316 patients will be recruited.

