**Trial registration number:**

ISRCTN13930454.

Strengths and limitations of this studyLargest randomised controlled trial of minimally invasive cardiac surgery globally.Strong and ongoing patient and public involvement and international clinical consensus informed trial design.Robust design, with 90% power, includes randomisation to surgery performed by consultant surgeons with defined expertise beyond the learning curve. Design requires some patients to move between surgeons, which may impact recruitment but assures quality of outcomes and reduces bias.Multicentre UK trial with blinding of central primary outcome assessor and echocardiogram core laboratory.Up to 5 year estimates of key clinical and survival outcomes.

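### Minor arithmetic error in the revised sample size: SD 26.3 needs 294 evaluable patients rather than 288, and 316 less 10% leaves 284, so unadjusted power is about 89%

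*Protocol article*

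**What the plan says.** The Sample size section of the Protocol article gives two calculations for the same target difference: "a minimally clinically important difference is 10 points on the scale".

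- **Original calculation:** "Assuming alpha of 5% and 90% power, 382 patients (191 in each arm) would be required", with the qualifier "assuming SD of 30".
- **Revised calculation:** this follows a "blinded sample size re-estimation using baseline SF-36v2 physical functioning scale data from 177 trial patients". The result is "Using the re-estimated SD of 26.3 with 90% power, 288 patients are required to detect a 10 point difference". The last step is "Accounting for 10% attrition, 316 patients will be recruited".

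The Setting section repeats 316 as the recruitment target, and the list of strengths and limitations describes a "Robust design, with 90% power". The aim is stated as superiority ("powered to investigate the superiority of thoracoscopically guided right minithoracotomy over conventional sternotomy"). The Sample size section does not say whether the 5% is one- or two-sided, which test was used, or how the attrition allowance was calculated. The Statistical analysis section plans a general linear model for the primary outcome that includes the baseline score.

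**The concern.** The two calculations differ only in the SD, so the method behind the first should give the second. It does not: 288 is too small for an SD of 26.3. The attrition sentence then conflicts with the one before it, because removing 10% of 316 leaves fewer patients than that sentence requires. Both discrepancies make the target slightly too low.

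The re-estimation is what reduced the planned number randomised from 400 to 316, so readers are likely to check this calculation. At stake is whether the published target and the 90% power can be traced to the stated inputs. The viability of the trial is not in question.

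**Working it through.** **Inputs.** From the Sample size section: difference 10 points, alpha 5%, power 90%, SD 30 (original) and 26.3 (revised), attrition 10%. From the Randomisation section: 1:1 allocation. Two-sided testing is inferred. It reproduces the original 382, whereas one-sided 5% would give 310 at SD 30.

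**Formula.** By the normal approximation, n per arm = 2 × (1.960 + 1.2816)² × SD² / 10², where (1.960 + 1.2816)² = 10.507. The exact version takes power from the noncentral t distribution with 2n − 2 degrees of freedom and uses the smallest n that reaches 90%.

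**Step 1: reproduce the original figure (SD 30).**
- Normal approximation: 2 × 10.507 × 900 / 100 = 189.1, so 190 per arm (380).
- t-test: 190 per arm gives 89.99% and 191 gives 90.1%, so 191 per arm (382).

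The t-test matches the article's 191 per arm exactly.

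**Step 2: the same method at SD 26.3.**
- Normal approximation: 2 × 10.507 × 691.69 / 100 = 145.4, so 146 per arm (292).
- t-test: 146 per arm gives 89.94% and 147 gives 90.1%, so 147 per arm (294).

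The stated 288 is 144 per arm. Rounding of the SD does not explain it. The smallest SD that rounds to 26.3 is 26.25, which needs 145 per arm by the normal approximation and 146 by the t-test. By the t-test, 144 per arm reaches 90% only if the SD is about 26.09 or less; by the normal approximation, only if it is about 26.18 or less. An SD of 26.0 gives exactly 288 by the t-test.

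**Step 3: the attrition allowance.**
- Needed to keep 288 after 10% loss: 288 / 0.9 = 320.
- Remaining from 316 after 10% loss: 316 × 0.9 = 284.4, about 284.
- Largest loss that leaves 288 of 316: 1 − 288/316 = 8.9%.
- A route that lands near 316: 288 × 1.1 = 316.8, rounded down. This is inferred, as no formula is printed.

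**Step 4: both corrections together.** 294 / 0.9 = 326.7, so 327 (t-test), or 292 / 0.9 = 324.4, so 325 (normal approximation).

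**Step 5: power at SD 26.3 for 10 points, two-sided 5%, unadjusted.**

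| Evaluable | t-test | Normal approximation |
|---|---|---|
| 294 | 90.1% | 90.3% |
| 288 | 89.5% | 89.7% |
| 284 | 89.1% | 89.3% |

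**Step 6: effect of the planned baseline adjustment.** Assume that 26.3 is also the SD of the 12-week score and that adjustment reduces the residual variance to SD² × (1 − r²), where r is the correlation between baseline and 12-week scores. With 142 per arm, 90% power needs a residual SD of about 25.9. Then 1 − (25.9/26.3)² = 0.03, so r is about 0.17. Under the same assumptions, power is 91.7% at r = 0.3 and 95.8% at r = 0.5. The article gives no value for r.

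**The case against.** The strongest reply is that the discrepancy is negligible. The stated 288 is within about 2% of the recomputed figure, 316 is 4 patients (1.3%) short of 320, and power falls by less than one percentage point. With 284 evaluable patients, 90% power is reached for a difference of 10.15 points instead of 10. The SD is far less certain than this: with 177 patients and roughly normal scores, its 95% interval is about 23.8 to 29.4. The calculation also takes no credit for the baseline adjustment in the planned analysis. Finally, the article does not print its attrition formula, adding 10% is a common if looser convention, and a fuller protocol may name the method.

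Most of this stands, and it is why the point is minor. It does not make the printed figures agree. No SD that rounds to 26.3 gives 288 by either standard method. The shortfall after attrition does not depend on how 316 was obtained, since 10% of 316 lost leaves fewer than 288 in any case. Baseline adjustment bears on the power the trial will actually have, not on a derivation that does not invoke it.

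A reader might infer that the trial fails to deliver its advertised 90% power. The documents do not support that. The unadjusted figure is about 89%, and the planned model needs only a weak correlation to make up the difference.

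**Conclusion.** The point holds as a minor arithmetic error. On the stated inputs, 294 evaluable patients are needed (292 by the normal approximation) instead of 288, and 316 recruited does not allow for 10% attrition from 288. The cost is about one percentage point of unadjusted power. The baseline-adjusted analysis probably recovers it, on the assumption of a correlation of about 0.17 or more.

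The conclusion rests on two-sided testing, inferred from the original 382, and on 26.3 being the SD intended. If the SD actually used was nearer 26.0, then 288 is right and the printed SD is wrong; the attrition discrepancy remains either way. Nothing here calls for a change to the design, the recruitment target or the analysis.

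**What to change.** Keep 316 and correct the text of the Sample size section:

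1. Check the re-estimation output. If 26.3 is right, change 288 to 294; if 288 came from a different SD, print that SD.
2. State that the test is two-sided, if that is confirmed.
3. Replace the attrition sentence with wording such as: 316 randomised with 10% attrition leaves about 284 evaluable, giving about 89% power for 10 points at SD 26.3 (two-sided 5%) before baseline adjustment. If a different SD is printed under item 1, recompute the power in this sentence.
4. Bring the 90% power in the strengths and limitations list into line, for example as about 89% before baseline adjustment.

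The cost is a few corrected figures and a stated power about one point lower. No extra patients are needed and no analysis changes.

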### Trial procedures

Patients due to undergo isolated MVr surgery at participating centres are identified at the point of referral (elective patients) and from the inpatient waiting list (urgent but non-emergency patients) by the clinical research team and approached about the trial, including given an information sheet and consent form. After discussion, consent is sought, baseline assessments performed and eligibility checked and confirmed by one of the consultant surgeons participating in the trial. Eligible patients are randomised, and their general practitioners informed. A full schedule of events is detailed in table 1, and a participant flow chart provided in figure 1. Patients have assessments at 6, 12, 18, 24, 38 and 52 weeks following index surgery. Longer term follow-up will involve routinely collected data.

**Table 1 T1:** UK Mini Mitral Schedule of Events

Study procedure	Baseline	Day of surgery	Index hospital stay	Follow-up: time is calculated from the day of index surgery					
	−26 weeks to day of surgery	Day 0	Day 0 until discharge following index surgery	6 weeks	12 weeks	18 weeks	24 weeks	38 weeks	52 weks
Consent	X								
Medical history	X								
Physical examination	X								
Demographics	X								
Concomitant medications	X			X	X				X
Pregnancy test	X								
NYHA class	X			X	X				
ECHO (TTE)	X		X	X	X				X
TOE	X	X							
SF-36v2	X			X	X	X	X	X	X
EQ-5D-5L	X			X	X	X	X	X	X
euroSCORE		X							
Accelerometer	X			X	X	X	X	X	X
Eligibility check	X								
Randomisation	X								
MVr surgery		X							
Postoperative details			X						
Wound Pain score			X^i^	X	X				
Ward usage and date of discharge			X						
Discharge destination			X						
RBC and other blood product transfusions		X	X						
AEs and SAEs		X	X	X	X	X	X	X	X
Reoperation/further surgery		X	X	X	X	X	X	X	X
Health Care Utilisation Questionnaire				X	X	X	X	X	X
HES data				X	X	X	X	X	X
NICOR data				X	X	X	X	X	X
Medical record review				X	X	X	X	X	X

AE, adverse event; ECHO, Echocardiogram; EQ-5D-5L, EuroQol 5 Dimension 5 Level; HES, Hospital Episode Statistics; MVr, mitral valve repair; NICOR, National Institute for Cardiac Outcomes Research; NYHA, New York Heart Association; RBC, Red Blood Celleuor; SAE, serious adverse event; SCORE, European System for Cardiac Operative Risk Evaluation; SF36-v2, Short Form Health Survey; TOE, transoesophageal echocardiography; TTE, transthoracic echocardiography.

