### Setting

Three hundred and sixteen patients due to receive MVr surgery will be recruited from UK NHS cardiothoracic surgery units with established minimally invasive and conventional mitral valve services. All centres will be able to accommodate the needs of this trial including established minimally invasive MVr services, research nurse and echocardiographer support, and facilities to carry out trial assessments. Only units in equipoise in the way they manage their patients requiring MVr will participate.

At each centre, individual surgeons perform one type of operation; MVr via thoracoscopically guided right minithoracotomy or MVr via median sternotomy. Before performing surgery within the trial, each surgeon has completed 50 of these; the Trial Steering Committee (TSC) reviews a record of the number of operations for each surgeon, and agrees to their participation, in advance of them doing so. Depending on their allocation, patients can be required to move to another surgeon following randomisation.

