### Statistical analysis

Primary analysis will follow intention to treat principles, with patients analysed according to randomisation, irrespective of surgical intervention received. A full statistical analysis plan will be developed and agreed with the Independent Data Monitoring and Ethics Committee (IDMEC) and TSC prior to the end of data collection.

Outcome data will be analysed at the end of the study; no interim outcome analyses are planned.

Primary analysis of change in physical functioning, measured using SF-36v2 at 12 weeks, will use a general linear model accounting for surgical intervention, baseline scores, valve pathology and concomitant surgery. Robust SE will account for intrapatient correlation due to repeated measures. A similar modelling approach will be used for the final analysis of change in physical functioning at 52 weeks.

Secondary outcomes: continuous outcomes will be analysed using a general linear model, binary outcomes will be analysed using a generalised estimating equation to account for repeated binary data over time, categorical outcomes (with more than two categories) will be analysed using baseline-category logit model, while log-rank test and frailty modelling will be used to analyse time-to-event outcomes. Analysis of all outcomes with repeated measures on the same patient will account for intrapatient correlation. Multiple imputation for secondary outcomes will be used if necessary to sensitise incomplete data. All outcomes will also be described using simple statistics to facilitate interpretation and communication of findings. Secondary analysis will also include hierarchical modelling of patients, surgeons and centres, to provide an estimate of treatment effect at each of these levels.

Each question within the SF-36v2 physical functioning scale will be scored based on the RAND scoring system.^42^ The average of the per-patient scale scores (assuming each question carries equal weight) will provide the primary outcome for physical functioning at 12 weeks.

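### Survival and safety are timed from surgery rather than randomisation, and no adverse-event collection is scheduled while patients wait, so a comparison of survival in all randomised patients should be added

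*Protocol article*

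**What the plan says.** All references are to the protocol article.

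- **Time zero.** The header of Table 1 (Trial procedures) reads "Follow-up: time is calculated from the day of index surgery". Randomisation is in the baseline column, whose window runs from minus "26 weeks to day of surgery".
- **Order of steps.** Consent, baseline assessments and the eligibility check come first; then "Eligible patients are randomised, and their general practitioners informed". Surgery follows.
- **Collection.** The adverse-event and reoperation rows are blank at baseline and begin on the day of surgery. The "Health Care Utilisation Questionnaire" row and the HES, NICOR and medical record review rows are first marked at 6 weeks after surgery.
- **Outcomes.** The list that holds survival, valve-related events, costs and QALYs is headed "Secondary outcomes post index MVr". Survival and events are compared at 52 weeks and up to 5 years. The primary outcome is a change "from baseline to 12 weeks following index surgery".
- **Surgeons.** Under Setting, each surgeon performs one type of operation and "patients can be required to move to another surgeon following randomisation".
- **Analysis set.** Under Statistical analysis, the primary analysis follows intention to treat, "with patients analysed according to randomisation, irrespective of surgical intervention received".

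**The concern.** Randomisation makes the arms comparable at the moment of allocation. Here the clock starts later, at an event that allocation may influence. The arms are served by different surgeons, and some patients must move to a new one once allocated. It is therefore plausible, though not shown, that one arm waits longer or has more patients who never reach surgery. Survival and safety timed from surgery would then compare those who reached surgery, after waits that may differ, instead of the randomised groups.

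A death or serious adverse event during the wait has no place on the schedule. If the expertise-based pathway lengthens the wait in one arm, any harm from that is a consequence of the allocated strategy, and the planned comparison would not show it. This matters most for overall survival up to 5 years, which the article lists among its strengths.

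**Working it through.** **1. The schedule, row by row (Table 1)**

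| Item | First scheduled point | Scheduled between randomisation and surgery? |
|---|---|---|
| Randomisation | Baseline column (−26 weeks to day of surgery) | n/a |
| SF-36v2, EQ-5D-5L | Baseline (before randomisation), then 6 weeks after surgery | No |
| AEs and SAEs, reoperation | Day of surgery | No |
| Health-care use, HES, NICOR, record review | 6 weeks after surgery | No |

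The text introduces Table 1 as the full schedule, so the start of collection is a stated rule and not merely a detail left out. The 26 weeks is the maximum for the whole baseline window. Randomisation is its last step, so the wait from randomisation to surgery lies somewhere between 0 and 26 weeks.

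**2. What the time origin does to a survival comparison**

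Let T be time from randomisation to death and W the wait. Randomisation protects the comparison of Pr(T > t) between arms. Timing from surgery compares Pr(T − W > t, given that surgery took place). The two can be relied on to agree only if W and the chance of reaching surgery do not depend on arm. The Setting section gives a route by which they could depend on it. The article gives no waiting times and no non-operation rates, overall or by arm, so the difference cannot be calculated.

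**3. The plan's own sample size**

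Inputs (Sample size section): difference 10 points, 90% power, alpha 5%, SD 30 originally and 26.3 after re-estimation. Two-sided testing is assumed because the article does not state it; one-sided totals would be 310 and 238 and do not fit.

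n per arm = 2 × (1.960 + 1.282)² × SD² / 10²

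- SD 30: 189.1, rounded up to 190 per arm, total 380 (382 with the t distribution). Stated: 382.
- SD 26.3: 145.4, rounded up to 146 per arm, total 292 (294 with the t distribution). Stated: 288, within 3%.
- Attrition of 10%: 288 × 1.1 = 316.8, or 288 / 0.9 = 320. Stated: 316. The allowance is 316 − 288 = 28 patients.

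The stated figures reproduce closely enough and do not bear on the point.

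**4. Effect of pre-operative loss on power (assumed rates)**

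Let p be the proportion never operated on and q the further loss after surgery. Evaluable N = 316 × (1 − p) × (1 − q), with m = N / 2 per arm. Power = Φ(10 / (26.3 × √(2/m)) − 1.96).

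| p | Patients not operated on | N, power with q = 5% | N, power with q = 10% |
|---|---|---|---|
| 2% | 6 | 294, 90.3% | 279, 88.8% |
| 5% | 16 | 285, 89.4% | 270, 87.8% |
| 10% | 32 | 270, 87.8% | 256, 86.0% |

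Power changes little. The issue is comparability of the arms and completeness of safety data.

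**5. Can the mortality effect be sized?**

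The only one-year mortality quoted is 0.7%, under Choice of comparators: 0.007 × 158 = 1.1 deaths per arm. It comes from patients who had minimally invasive surgery. It suggests that deaths will be few, so that a handful while waiting could matter, but it says nothing about how many such deaths there would be or in which arm.

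**The case against.** The strongest defence is that a surgical time origin suits this trial. The question is recovery after two operative approaches, and surgical events and their sequelae cannot precede surgery. That stands for the primary outcome and for the surgical and recovery outcomes, which should keep their origin. It does not stand for overall survival or for the recording of serious adverse events.

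Three stronger readings are tempting, and the article does not support them.

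- A reader might infer that patients who die or withdraw before surgery are excluded, or lost from every analysis. Nothing says so. HES and NICOR are routine data, and a mark at 6 weeks does not show that earlier records are unavailable. Handling of unoperated patients may be set out in the full protocol or SAP, which are not shown. Nor are all outcomes timed from surgery: recruitment and feasibility are not.
- A reader might infer that the survival, safety and cost comparisons contradict the intention-to-treat statement. That sentence is written for the primary analysis only. An unoperated patient has no 12-week date, which sits awkwardly with it, but this is no contradiction about survival, safety or cost.
- A reader might take 26 weeks as the usual wait, or take separate surgeons to mean separate waiting lists with different delays. The first is a maximum, and the second is not described anywhere.

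It is also fair to say that recruitment is well advanced: 177 patients had supplied baseline data by the re-estimation, so a new starting point for event reporting would be a change in mid-trial. That limits the remedy without removing the case for it.

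**Conclusion.** The point holds in a limited form. The schedule fixes time zero at surgery, begins adverse-event collection there, and defines survival, events, costs and QALYs after it, while the surgeon arrangements make arm-dependent waiting or non-operation plausible. If either differs by arm, survival and safety comparisons timed from surgery are not protected by randomisation, and events on the waiting list go unscheduled.

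The size of any bias is unknown, because the article gives no pre-operative loss rate and no waiting times. Under assumed pre-operative loss of 2% to 10%, power stays at about 88% to 90% with a further 5% later loss, and at 86% or above with a further 10%. This is a cheap improvement worth making, not a flaw that undermines the primary result.

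**What to change.** 1. Analyse overall survival at 52 weeks and up to 5 years from randomisation in all randomised patients, and report the from-surgery analysis beside it.
2. Record deaths and serious adverse events from randomisation. For patients already enrolled, use the planned HES and NICOR data and the medical record review to cover the wait.
3. Report, by arm, the time from randomisation to surgery and the number not operated on.
4. Keep the primary outcome at 12 weeks after surgery, and keep the surgical and recovery outcomes timed from surgery.
5. Do not adjust outcome models for time from randomisation to surgery. It arises after allocation and may depend on arm, so adjusting for it could introduce bias.

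The cost is analysis wording, an instruction to sites, and a few extra serious adverse event reports. Capture will be less complete for patients enrolled before the change, and the report should say so.
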